### Known Potential Benefits

All individuals participating in this research will benefit by having a thorough baseline psychological assessment as well as potentially effective intervention which may result in a decrease in suicidal risk. The potential benefits to individuals outweigh potential risks, particularly in offering them the chance to better understand the nature of their suicidal behavior and to receive a baseline psychological evaluation. On a larger scale, the information obtained from this study will further our understanding of how to treat adolescents who attempt suicide.

### Assessment of Potential Risks and Benefits

Risk associated with participation in the study is low. Study participation will provide patients with additional clinical care and assessment without additional cost. Research on preventing future suicide attempts in high-risk groups is greatly needed due to the prevalence of the problem and the lack of extensive research in this area. Therefore, the benefits are anticipated to exceed the risks for participants.

# OBJECTIVES AND ENDPOINTS

| OBJECTIVES | ENDPOINTS | JUSTIFICATION FOR ENDPOINTS | PUTATIVE MECHANISMS OF ACTION |
| --- | --- | --- | --- |
| Primary |  |  |  |
| To examine the effectiveness of STEP in reducing suicidal events (suicide attempt or emergency intervention to intercede attempt, i.e. ED evaluation or psychiatric hospitalization), active suicidal ideation (with intent or plan), and depression, compared to ETAU. | Suicidal events and active suicidal ideation as assessed by the Columbia-Suicide Severity Rating Scale (C-SSRS) interview, and depression as assessed by the Beck Depression Inventory (BDI-II) at 6 month follow-up (primary endpoint) and suicidal events at 12 month follow-up (secondary endpoint) | Six-month follow-up is selected as the primary end-point time as numerous studies have shown this to be a particularly high-risk time for repeat suicidal behaviors. Twelve months allow us to assess the long-term effectiveness. | NA |
| Secondary |  |  |  |
| To examine engagement of the hypothesized mechanisms of positive affect (PA) and negative affect (NA). | Attention to PA and NA as assessed by implicit cognitive tasks and self-report forms (See 1.3) at 3 month follow-up (primary) and 6 month follow-up (secondary) endpoint. | PA and NA are hypothesized to be causal mechanisms. Thus these assessments will see if we engaged our treatment target of PA and NA. | PA and NA are hypothesized to be causal mechanisms. |
| Tertiary/Exploratory |  |  |  |
| To examine whether hypothesized mechanisms mediate reduction of suicidal events and ideation. | Attention to PA and NA as assessed by implicit cognitive tasks and self-report forms (See 1.3) at 3 month follow-up (primary) and 6 month follow-up (secondary) endpoint. | The PA and NA assessments, using both implicit and subjective assessments, will be examined as mediators. Specifically, PA and NA at 3 month f/u is hypothesized to mediate the relationship between study intervention and clinical outcomes at the 6 month f/u; and PA and NA at 6 month f/u is hypothesized to mediate the relationship between study intervention and clinical outcomes at the 12 month f/u. | PA and NA will be examined as mediators. |

# STUDY DESIGN

## Overall Design

This is a randomized controlled trial (RCT) of Skills to Enhance Positivity (STEP) vs. Enhanced Treatment as Usual (ETAU). It is hypothesized that those randomized to STEP, compared to ETAU, will have lower rates of suicide events, active SI, and depression over the 6-month follow-up period (primary endpoint), and over 12 months of follow-up (secondary endpoint). Recruitment will occur at three sites, Boston Children’s Hospital, Butler Hospital, and Bradley Hospital. Eligible individuals who consent to participate will be randomly assigned to either STEP or ETAU in a 1:1 allocation after the baseline assessment. Co-I [name] will prepare a stratified [by study site, history of SB (yes/no), and sexual or gender minority (yes/no)} randomization schedule using random blocks and provide this to our REDCap administrator; study staff will not have access to randomization tables). Research staff will be able to obtain assignments in real time once consent and stratification variable information are recorded. We use random block sizes to prevent guessing of pending treatment assignments.

The study intervention, Skills to Enhance Positivity (STEP), is an adjunctive psychosocial intervention that involves 4 in-person sessions during a participant’s inpatient admission, followed by three months of text or email messaging for mood monitoring and skills delivery. (If participant has a shorter length of stay or is discharging early, the STEP sessions may be shortened so that the intervention can be delivered prior to discharge). The sessions and skills delivered via the text or email messages focus on the functions of positive affect and ways to bring greater attention to and awareness of positive emotions and experiences on a daily basis. Four videos with content derived directly from the treatment manual will be used to support the delivery of the STEP skills that are covered in the in-person sessions.

Parents/guardians will be provided with a handout containing information about the study, contact information, and details on how they can best support their child throughout the duration of the study. The comparison condition (ETAU) consists of treatment as usual on the unit which is enhanced by discharge plan which includes reminders of their safety plan and that key phone numbers (supports, suicide hotlines) are preprogrammed for easy access. Participants will receive the messages on a daily basis for 30 days with reminders that their safety plan and phone numbers are on their phone. ETAU participants will also receive reminders to practice some Healthy Habits and reminders to look at their safety plan. Similar to the STEP condition and as a means to control for contact time, after 30 days, ETAU participants will be placed on a tapered schedule of receiving alerts 3 times per week for an additional 60 days.

**Primary Aims are described above under Section 3, Objectives and Endpoints. There is an additional secondary aim which reads as follows:**

*Examine elements supporting external validity*. Acceptability, appropriateness, and feasibility of STEP to patients, parents, clinicians, and inpatient unit administrators will be assessed by: 1) a survey consisting of brief, standardized measures of these items, and 2) qualitative interviews to further explore these perceptions. This will be assessed pre-implementation of the RCT to enhance the feasibility of our trial (details of the pre-implementation phase are not discussed in this document because they precede the RCT), and post-RCT implementation to ascertain facilitators and barriers. These findings will be used to: 1) modify STEP to address potential barriers, and 2) develop implementation strategies designed to overcome these challenges for testing in a future Hybrid Type III effectiveness-implementation trial. The measures used in post-RCT implementation are listed above in the measures chart. Providers, adolescents and guardians will participate in qualitative interviews and complete self-report measures (about intervention acceptability, appropriateness, feasibility, as outlined at baseline and varying schedules at the 3, 6, and 12-month follow-up assessments). Providers only will complete additional measures at baseline, 6, and 12-month follow-ups. These self-report measures will examine evidence-based practice attitudes, implementation complete, and implementation readiness.

## Scientific Rationale for Study Design

The study design is an RCT comparing the study intervention to an enhanced treatment as usual condition. All participants receive equivalent inpatient care with the exception of receiving either STEP sessions or. TAU therapy sessions, depending on the condition to which they are designed. STEP participants will be pulled from regular therapeutic programming for their 4 STEP sessions (while ETAU will be in therapy sessions). After discharge, ETAU get prompts to remind them of their safety plan or practice a Healthy Habit with the same frequency as STEP participants. Both conditions receive the exact same assessments and the passage of time is equivalent. Therefore, we do not anticipate any problems associated with the control group in light of participants’ risk for suicidal behavior, as they will continue to receive ongoing treatment on the inpatient unit and are able to engage in outpatient treatment after discharge.

## Justification for Intervention

STEP involves four in-person sessions on the inpatient unit, as well as remote delivery via text or email for three months post-discharge. Testing a protocol that is delivered during inpatient hospitalization maximizes the use of frontline milieu staff to deliver a low-cost intervention. The use of multiple modes of delivery, i.e., an in-person delivery phase, to occur on the inpatient unit, combined with a remote delivery phase, to occur upon discharge to their home environment, facilitates engagement with high-risk youth who may encounter barriers to subsequent care, through low-cost, broadly accessible means. The number of sessions and duration of intervention is informed by feedback from a prior pilot trial of this intervention. The minimum-acceptable participation will be defined as one in-person session and any engagement with the text/email messaging program. To accommodate participants who might have a shortened length of stay in the hospital, the STEP sessions might be compressed at times so that teens have the complete intervention delivered prior to discharge. If teens have their phones taken away, parents will be asked to allow their child to access the text messages from the STEP protocol when they are received at a pre-specified time (at the same time each day) for a time-limited duration, for the purposes of the study protocol. Alternatively, if it is not possible for the teen to have access to their phone, participants will instead receive the messages through email and REDCap.

## End-of-Study Definition

A participant is considered to have completed the study if he or she has completed the baseline assessment, and the 6-month and 12-month follow-up assessments.

The end of the study is defined as completion of the 12-month follow-up assessment shown in the Schedule of Activities (SoA), **Section 1.3**.

# STUDY POPULATION

The primary study population is adolescents psychiatrically hospitalized due to suicidal ideation or behavior. Parents will also be enrolled as study participants because they are asked to participate in study assessments, they will solely be informants of their child’s symptoms and experiences. All recruitment sites (Butler Hospital, Bradley Hospital, and Boston Children’s Hospital) have a broad payor mix and include Medicaid and uninsured patients. These participants (and their guardians) are described below.

In addition, at the end of the trial, acceptability, appropriateness, and feasibility of STEP to clinicians, and administrators will be assessed by: 1) a survey consisting of brief, standardized measures of acceptability, appropriateness, and feasibility, and 2) qualitative interviews to further explore these perceptions. These findings will be used to: 1) modify STEP to address potential barriers, and 2) develop implementation strategies designed to overcome these challenges for testing in a future Hybrid Type III effectiveness-implementation trial.

## Inclusion Criteria

In order to be eligible to participate in this study, an individual must meet all of the following criteria:

1. Provision of signed and dated informed consent form
2. For children, informed assent and parental informed consent to participate in the study
3. Age 12-18 years
4. Hospitalized on an inpatient psychiatric unit due to suicide risk (attempt, ideation, threat) as noted in the Admission note
5. Past-month attempts or ideation as verified by the Columbia Suicide Severity Rating Scale interview
6. Willingness to adhere to the STEP regimen
7. Participants must have access to their own phone.
8. Participants must be proficient in English, and a parent fluent in either English or Spanish

## Exclusion Criteria

An individual who meets any of the following criteria will be excluded from participation in this study:

1. Acute psychotic disorders or cognitive deficits that would preclude full understanding of the protocol, intervention, and assessment materials. Determination of mental status as it relates to patients’ ability to fully participate in this study will be based on chart review and consultation with unit psychiatrists. Similar criteria will be used if cognitive deficits or psychosis symptom occur at follow-up appointments. The research team will assess whether these deficits would preclude full understanding of the assessment protocol. If so, they will be withdrawn. We anticipate that most participants will remain in the study because fleeting cognitive symptoms may occur in disorders other than psychosis spectrum disorders.
2. Patients who are admitted from, or have a planned discharge to, a residential treatment facility will be ineligible. However, those admitted to residential treatment *after* enrollment in our study will remain in the study.

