# STUDY INTERVENTION/EXPERIMENTAL MANIPULATION DISCONTINUATION AND PARTICIPANT DISCONTINUATION/WITHDRAWAL

## Discontinuation of Study Intervention/Experimental Manipulation

When a subject discontinues from the study intervention, whether voluntarily or involuntarily, but not from the study, remaining study procedures will be completed as indicated by the study protocol. If a clinically significant finding is identified (including, but not limited to changes from baseline) after enrollment, the investigator or qualified designee will determine if any change in participant management is needed. Any new clinically relevant finding will be reported as an adverse event (AE).

The data to be collected at the time of study intervention discontinuation will include the following:

- The reason(s) for discontinuing the participant from the intervention, and methods for determining the need to discontinue
- If the participant is due to complete assessments within 2 weeks of being discontinued from the study intervention, those assessments will be administered at the time of discontinuation; if the next scheduled assessments are more than 2 weeks from the discontinuation date, the discontinued participant will wait for the next scheduled assessment. Thereafter, the participant will be included in all future scheduled assessments, even though not participating in the intervention.

A participant may be involuntarily discontinued from the study intervention if the participant has an unexpected adverse reaction to intervention content, develops psychiatric symptoms that make continuation of the intervention impossible, or if clinical staff deem it is not clinically appropriate to continue the intervention during the psychiatric admission. The participant will also no longer receive the messages, if they are discontinued from the study.

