## Participant Discontinuation/Withdrawal from the Study

Participants are free to withdraw from participation in the study at any time upon request.

An investigator may discontinue a participant from the study for the following reasons:

- Significant study intervention non-compliance, i.e. with respect to the individual sessions, unless varying compliance is an aspect of the study objectives
- Lost-to-follow up; unable to contact subject (see **Section 7.3, Lost to Follow-Up**)
- Any event or medical condition or situation occurs such that continued collection of follow-up study data would not be in the best interest of the participant or might require an additional treatment that would confound the interpretation of the study
- The participant meets an exclusion criterion (either newly developed or not previously recognized) that precludes further study participation

The reason for participant discontinuation or withdrawal from the study will be recorded on the Case Report Form (CRF). Subjects who sign the informed consent form and are randomized but do not receive the study intervention may be replaced. Subjects who sign the informed consent form, and are randomized and receive the study intervention, and subsequently withdraw, or are discontinued from the study, will not be replaced.

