***Sample size and statistical power considerations***. The power to test the difference between two proportions, .17 and .38, is significantly different from zero can be found from POWER = F(sqrt(((n*(p1-p2)^2)/(p0*(1-p0)))/2) – F’(1-(a/2))), where F is the cumulative normal density function and F’ is the normal quantile function, a is the desired type-I error level, n is the per-group sample size and p1 and p2 are the target proportions. H1A and H1D have similar minimum detectable effect sizes because we use a conservative estimate of the within-person correlation of propensity to suicide for aims H1A-H1C. We conservatively use 162 as our sample size for these calculations but we expect to have a larger sample with suicidal event data because these data can be drawn from the electronic health record in addition to participant self-report.

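### Exclusion criterion 1 is re-applied at follow-up and ends study participation, although guardian and hospital-record outcome data could still be collected

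*Protocol*

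**What the plan says.** Criterion 1 of the Exclusion Criteria first screens out acute psychosis and cognitive deficits at entry. It then extends past randomization: "Similar criteria will be used if cognitive deficits or psychosis symptom occur at follow-up appointments". The consequence is mandatory: "The research team will assess whether these deficits would preclude full understanding of the assessment protocol. If so, they will be withdrawn". The next sentence shows that this means leaving the study, not skipping an instrument: "We anticipate that most participants will remain in the study because fleeting cognitive symptoms may occur in disorders other than psychosis spectrum disorders".

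Section 7.2 (Participant Discontinuation/Withdrawal from the Study) lists reasons for which an investigator may discontinue someone, among them: "The participant meets an exclusion criterion (either newly developed or not previously recognized) that precludes further study participation".

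Two other places point the other way. Criterion 2 says that those who enter residential treatment after "enrollment in our study will remain in the study". Section 7.1 deals with a participant who "discontinues from the study intervention, whether voluntarily or involuntarily, but not from the study", and one of its triggers is new psychiatric symptoms that rule out carrying on with the intervention. Of such participants it says: "Thereafter, the participant will be included in all future scheduled assessments, even though not participating in the intervention".

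Section 9 commits the analysis to intent-to-treat principles, with multiple imputation and sensitivity analyses. On suicidal events, it expects more data than the 162 participants assumed for power because "these data can be drawn from the electronic health record in addition to participant self-report".

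**The concern.** An exclusion criterion defines who may be randomized. Used again afterwards, it lets a clinical state that arises during follow-up decide whose outcomes are observed. If participants with emergent psychosis or disabling cognitive symptoms have a different risk of suicidal events from the rest, their absence is informative. Imputation under a missing-at-random assumption would not fully correct that.

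The loss is largely avoidable. The rule exists because the adolescent cannot understand the assessments, but several planned sources of primary-outcome data do not depend on the adolescent. No section says whether those sources continue once an investigator has withdrawn a participant. Staff following the text as written could reasonably stop all collection. At stake are a small number of outcomes from participants whose course is of particular interest, and consistent handling across sites, since one section says such participants will leave and another says they may.

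**Working it through.** **1. The rules side by side**

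| Place | Trigger | Force | Consequence |
|---|---|---|---|
| Exclusion Criteria, criterion 1 | Psychosis or cognitive deficit at follow-up that prevents understanding of the assessments | Mandatory | Leaves the study |
| Section 7.2 | Exclusion criterion newly met or newly recognized, if it precludes further participation | Discretionary | Leaves the study |
| Section 7.1 | New psychiatric symptoms that rule out the intervention | Discretionary as to the intervention | Remains in all later assessments |
| Exclusion Criteria, criterion 2 | Residential placement after enrollment | Mandatory | Remains in the study |

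The triggers in rows 1 and 3 are not identical, but they overlap: a psychotic episode during the three-month messaging phase could meet both. The consequences for outcome collection are then opposite. Rows 1 and 2 differ in force for the same participant.

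**2. Outcome sources that do not need the adolescent**

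- Guardian C-SSRS at 3, 6 and 12 months (Schedule of Activities): suicidal events and ideation.
- Guardian BDI-II at 3 and 6 months (Schedule of Activities): depression. The protocol does not say which informant's score is the endpoint. Even if it is the adolescent's, the guardian score can inform the imputation.
- Record audit of ED and inpatient admissions at the three hospitals, under a consent permission that runs for the duration of the study (Strategies for Recruitment and Retention).

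Guardians are enrolled as informants in their own right (Study Population) and are assessed separately from the adolescent (Participant Incentives).

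**3. Power is not the problem**

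Inputs from Section 9 (Aim 1D): event rates 38% and 17%, 162 analysed, so n = 81 per arm, stated power 80%. I assume two-sided alpha 0.05 and take p0 as the mean rate, 0.275.

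The printed formula gives sqrt[(81 × 0.21²)/(0.275 × 0.725)/2] − 1.96 = 2.993 − 1.960 = 1.033, that is 84.9%. A continuity-corrected calculation gives 81.1% and Fisher's exact test 81.7%, so the stated 80% is reproduced by those variants. If 10% of the 162 were lost to this rule (n = 72.9 per arm), the printed formula still gives 81.0%.

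**4. What withdrawal could do to the estimate (illustration only)**

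The documents give no withdrawal rate and no event risk for those withdrawn, so both are assumed here. With true rate p, fraction withdrawn w and event risk q among them, the rate in those retained is (p − wq)/(1 − w). The true difference is 38 − 17 = 21.0 points.

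| Withdrawn ETAU / STEP | q | ETAU retained | STEP retained | Difference (points) |
|---|---|---|---|---|
| 3% / 3% | 80% | 36.7% | 15.1% | 21.6 |
| 2% / 6% | 50% | 37.8% | 14.9% | 22.9 |
| 2% / 6% | 80% | 37.1% | 13.0% | 24.2 |
| 2% / 6% | 100% | 36.7% | 11.7% | 25.0 |
| 6% / 2% | 50% | 37.2% | 16.3% | 20.9 |
| 6% / 2% | 80% | 35.3% | 15.7% | 19.6 |
| 6% / 2% | 100% | 34.0% | 15.3% | 18.7 |

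Differences are from unrounded rates. The sign of the shift follows the assumed imbalance, and nothing in the documents favours one direction. With 216 randomized 1:1, 2% and 6% of an arm of 108 are about 2 and 6 participants. These are complete-case figures; record data and imputation would reduce the shifts.

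**The case against.** The strongest reply is that the rule is narrow, expected to bite rarely, and protective: ending research procedures for someone who can no longer understand them is defensible. Participants may be 18 and consent for themselves, so continuing to interview a guardian or read records about such a person raises a consent question. That stands, and the remedy has to deal with it.

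Several stronger readings are tempting but are not supported:

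- *The protocol contradicts its own retention rule.* Section 7.1 covers people who stop the intervention and stay in the study. Section 7.2 openly allows study discontinuation, at the investigator's discretion and only where the criterion precludes further participation. This is tension between overlapping triggers. Nor is there a true conflict over residential treatment, because criterion 2 expressly keeps those placed after enrollment.
- *The sickest participants are removed.* The rule reaches psychosis or cognitive deficits that prevent understanding. Severe suicidality, depression or re-hospitalization does not by itself trigger it.
- *STEP participants would be withdrawn more often because their sessions give more chances to notice.* STEP sessions replace other unit activities, with no additional therapeutic contact intended (Administration and/or Dosing). At follow-up both arms receive the same assessments from a blinded evaluator. No mechanism for an imbalance is documented.
- *The outcome data are certainly lost.* The protocol is silent on guardian and record data after withdrawal. Intent-to-treat with multiple imputation would keep the participant in the analysis, and sensitivity analyses are planned.

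What none of this answers is the silence itself. Imputing an outcome that a guardian or a hospital record could have supplied is second best.

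**Conclusion.** The point holds in a limited form. An eligibility criterion is re-applied after randomization, and as written it ends study participation on the basis of a post-randomization clinical state, with no statement that outcome collection from other sources continues. This fits poorly with intent-to-treat and with the approach taken in section 7.1. The risk is informative missingness in a small number of participants.

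Its size and direction cannot be determined from the documents. The shifts in the table, from 2.3 points down to 4.0 points up on a 21-point difference, rest entirely on assumed withdrawal rates and event risks and should not be read as estimates. The power statement is unaffected. The change is worth making because it is cheap and uses sources that are already planned.

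**What to change.** Reconcile criterion 1 of the Exclusion Criteria with sections 7.1 and 7.2, for outcome collection only:

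1. State that exclusion criteria govern entry up to randomization.
2. In criterion 1, replace the withdrawal sentence with a rule that, if an adolescent cannot understand the assessments at a visit, only the adolescent measures are skipped and recorded as missing for that visit. The participant stays in the study and the adolescent measures resume when feasible.
3. State that guardian assessments, as scheduled, and the record audit continue to 12 months unless consent is withdrawn.
4. Amend the exclusion-criterion bullet in section 7.2 to agree with items 1 to 3, which also removes the difference between mandatory and discretionary wording.
5. Confirm that the consent forms cover item 3 for participants who are 18 or turn 18 during the study.

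The cost is a protocol wording amendment and a consent-wording check. The downside is that some adolescent measures will be missing while the participant remains enrolled. No new assessments or data sources are needed.
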